### Present study

#### The objectives of the present study are to investigate

i.Whether chemotherapy is related to long-term attenuation of gut microbiota alpha diversity (i.e. gut dysbiosis, and which species differ significantly between patients and healthy controls);ii.Associations between gut microbiota, body composition (i.e. fat mass and lean mass, body fat percentage, and bone mineral concentration), inflammatory cytokine biomarkers (IL-6, IL-1B, TNF-a, IL-10), C-reactive protein (CRP), lipopolysaccharide (LPS), serotonin (5-HT), brain derived neurotrophic factor (BDNF), and cortisol;iii.Associations between gut microbiota, and psychological and cognitive outcomes including anxiety, depression, PTSD symptoms, pain, fatigue, and social and cognitive functioning;iv.Relationships between demographic and clinical factors, gut microbiota, and physiological, psychological and cognitive outcomes for survivors.

We hypothesize that:
i.Chemotherapy will be associated with significant reductions in gut microbiota alpha diversity at all time points, and relative to healthy controls;ii.Gut dysbiosis will be associated with increased risk for overweight/obesity, elevated pro-inflammatory cytokines, CRP and LPS, reduced serotonin and BDNF, and augmented levels of cortisol in survivors;iii.Gut dysbiosis will be associated with increased anxiety, depression, PTSD symptoms, pain, fatigue, and social and cognitive deficits in survivors;iv.There will be relationships between certain clinical factors (e.g. mucositis, antibiotic use), gut microbiota alpha diversity, and physiological, psychological and cognitive outcomes.

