##### Sample size and power

Target sample sizes of at least *n* = 50 cancer survivors and *n* = 50 healthy controls were selected based on sample sizes from previous studies on gut microbiota in cancer patients [17, 18] and practical considerations given the timeline and availability participants. With this sample size (*n* = 100 total), a medium effect size for group differences (Cohen’s d = 0.5, estimated with a power of 0.80, alpha = 0.05) can be detected using a one-sided test of the primary hypothesis that cancer survivors will have lower alpha diversity relative to controls [46].

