### Data analysis

*Objective 1* will examine whether chemotherapy is related to long-term gut dysbiosis as indicated by reduced alpha diversity in patients relative to controls, and from time points 1 through 3. Gut microbiota alpha diversity will be evaluated with the Shannon and Chao1 indexes using QIIME. To further examine differences in bacterial composition between the groups, LEfSe (linear discriminant analysis effect size) will be used to evaluate differential abundance between patients and controls, allowing us to identify the key bacteria that contribute most to the chemotherapy group having different bacteria relative to healthy controls. Linear Mixed Modelling (LMM) analyses will be used to examine differences across time and between groups. Group (survivors vs. healthy controls) and time (T1 – T3) will be fixed factors and individual subject will be a random factor.

*Objective 2* will first test group differences in gut microbiota, cytokines, LPS, 5-HT and BDNF, cortisol, and body composition using LMM as described above. We will test the interplay between the physiological systems of our model by examining associations between the gut microbiota, cytokines, LPS, 5-HT and BDNF, cortisol, and body composition using univariate correlations. Then multivariate regression models regressing cytokines, cortisol and body composition on gut microbiota diversity will be conducted, including variables that showed significant univariate correlations in the modelling. Covariates included theoretically based on the literature will include type of cancer diagnosis (i.e. blood or solid tumor), history of mucositis, glucocorticoid medication, antibiotic, and probiotic use, birth delivery mode, and breastfeeding in infancy.

*Objective 3* will first test group differences in cognitive and psychological parameters, gut microbiota diversity, and levels of 5-HT and BDNF using LMM as described above. We will test the relationships between gut microbiota, 5-HT and BDNF, and cognitive and psychological parameters using univariate correlations. Then multivariate regression models regressing psychological and cognitive parameters on gut microbiota diversity will be conducted, including variables that showed significant univariate correlations in the modelling. Covariates included theoretically based on the literature will as specified in objective 2.

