## Conclusion

Knowing what bacterial species are depleted after chemotherapy, how long these effects last, and the physiological mechanisms that may drive psychological and cognitive issues among survivors is a crucial step forward in gut microbiota and young adult cancer research. Understanding the bio-behavioural mechanisms that drive psychological and cognitive dysfunction among survivors will allow for tailored interventions to be developed. Future studies can aim to aid cancer patients and survivors by co-administering specific health promoting bacteria (i.e. probiotics), with the potential of preventing or reversing physical and mental health issues that many young survivors face.

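### The Objective 1 mixed model names group and time but no group-by-time term or visit contrast, so as written it cannot show at which visits diversity is lower or whether the gap lasts to 5–6 months

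*Protocol article*

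**What the plan says.** Hypothesis (i), in the Present study section, reads: "Chemotherapy will be associated with significant reductions in gut microbiota alpha diversity at all time points, and relative to healthy controls". The Data analysis section frames Objective 1 as a question about long-term dysbiosis, judged against controls and over the three visits (T1 under 2 months, T2 at 3–4 months, T3 at 5–6 months after chemotherapy). It then gives the linear mixed model: survivor or control group, and time, "will be fixed factors and individual subject will be a random factor". No interaction and no visit-specific comparison is mentioned. Objectives 2 and 3 begin with group differences from the same model.

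The Sample size and power section sets "Target sample sizes of at least *n* = 50 cancer survivors and *n* = 50 healthy controls". It gives the detectable effect as "Cohen’s d = 0.5, estimated with a power of 0.80, alpha = 0.05" and ties it to a "one-sided test of the primary hypothesis that cancer survivors will have lower alpha diversity relative to controls". It names no visit.

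The Conclusion describes what such knowledge is for: "Knowing what bacterial species are depleted after chemotherapy, how long these effects last".

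**The concern.** The question is about course: whether the survivor-control gap is there at each visit, and whether it is still there at 5–6 months. A model with group and time alone forces the gap to be the same at every visit and estimates one average.

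A gap that is wide soon after chemotherapy and gone by T3 can then produce the same significant group effect as a gap that never closes. A reader could take either as evidence of long-term dysbiosis. The time effect does not help, because it averages survivors with people who had no chemotherapy.

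A second, smaller matter is that the hypothesis is worded in two ways. The power section refers to lower diversity than controls; hypothesis (i) refers to all time points. The 0.80 belongs only to the comparison in the power section.

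**Working it through.** **Inputs from the protocol article.** 50 survivors and 50 controls; d = 0.5; one-sided alpha 0.05; three visits; group and time fixed, subject random.

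**Assumptions, not in the document.** Within-person correlation ρ equal between all pairs of visits; the pattern of true gaps over visits; no missing samples; survivors and controls independent.

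**1. The plan's own figure.** The noncentrality is d·√(n/2) = 0.5·√25 = 2.5. With 98 degrees of freedom and a one-sided 0.05 test, the noncentral t gives power 0.799. The normal approximation gives Φ(2.5 − 1.645) = 0.804. The stated 0.80 reproduces for one comparison. (A two-sided test would give 0.697.)

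**2. What the group effect estimates.** With complete data and no interaction, the group coefficient is the mean of the three visit gaps:

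- persistence: (0.5 + 0.5 + 0.5)/3 = 0.5
- recovery by T3: (1.0 + 0.5 + 0)/3 = 0.5

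The two histories are indistinguishable in this coefficient.

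**3. What the time effect estimates.** Suppose controls are flat and survivors recover by 1.0 SD from T1 to T3. With equal groups the pooled change is (1.0 + 0)/2 = 0.5, half of the survivors' change.

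**4. How often the averaged effect is significant.** The variance of a person's three-visit mean is (1 + 2ρ)/3 of the single-visit variance. Power is Φ(2.5/√[(1 + 2ρ)/3] − 1.645):

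| ρ | (1 + 2ρ)/3 | Power, averaged group effect |
|---|---|---|
| 0.3 | 0.533 | 0.96 |
| 0.5 | 0.667 | 0.92 |
| 0.7 | 0.800 | 0.875 |
| 0.9 | 0.933 | 0.83 |

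By step 2 these values hold for both histories. In the recovery pattern with ρ of 0.5 to 0.7, the group effect is significant in about 88–92% of studies although the T3 gap is zero.

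**5. Significance at all three visits.** Take d = 0.5 at each visit, 50 + 50 complete. The three test statistics are treated as trivariate normal with mean 2.5 and correlation ρ, and each must exceed 1.645:

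| ρ | Power, all three visits | Per group for 0.80 |
|---|---|---|
| 0.3 | 0.58 | 75 |
| 0.5 | 0.62 | 72 |
| 0.7 | 0.66 | 67 |
| 0.9 | 0.73 | 60 |

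**6. A change in the gap.** With the interaction in the model, the T1-versus-T3 difference in gap has variance 4(1 − ρ)/50 in SD² units (two groups of 50, each contributing 2(1 − ρ)/50). If the gap closes from 0.5 to 0, two-sided 0.05 power is 0.56, 0.71 and 0.90 at ρ = 0.3, 0.5 and 0.7. If it only halves, power is 0.18, 0.24 and 0.37.

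**The case against.** The strongest reply is that the article lists factors, not model terms. It neither includes nor excludes an interaction, and a condensed article may leave that to the full plan. This stands in part: a reader might infer that the study has committed to a main-effects-only model, and the text does not go that far. But the article does set out the model, with its fixed and random parts, and omits the one term that Objective 1 turns on. Objectives 2 and 3 inherit the omission.

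A reader might also infer that the 0.80 is wrong or overclaimed. It is neither. It is tied to one group comparison, reproduces for it, and is never claimed for all visits. If d = 0.5 holds at each visit with complete data, the averaged effect has 0.83 to 0.96 power, so 0.80 is conservative for it. Nor does the article make three simultaneous significant tests a success criterion; that is one reading of hypothesis (i).

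The recovery pattern and the correlations are assumptions. In that pattern survivors really are lower at T1 and T2, so a significant group effect is not false for the hypothesis as the power section words it. The error would lie in calling it long-term, and the article does not say that it would be reported so. The sentence in the Conclusion about duration concerns bacterial species and the value of the knowledge, so it is weak evidence about this model.

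Finally, the Discussion calls the study exploratory. That lowers the weight of the power figures, and it argues against insisting on T3 as the sole primary contrast. It does not remedy a model that cannot tell recovery from persistence.

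**Conclusion.** The point holds as a gap between question and model. Fitted with the terms named, the model returns one visit-averaged gap and one pooled time course. It cannot support a statement about each time point or about persistence to 5–6 months. That conclusion needs no assumed correlation; it follows from the averaging, illustrated by two assumed histories that both give 0.5.

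The power part is a matter of scope. The 0.80 is right for one one-sided contrast with 50 + 50 complete. It would be about 0.58 to 0.73 for significance at all three visits, assuming d = 0.5 at each visit, no loss of samples and ρ between 0.3 and 0.9. Missing samples would lower these figures.

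This is a cheap improvement worth making before analysis. It is not a must-fix, because an interaction is not ruled out and no stated figure is in error.

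**What to change.** - In Data analysis, Objective 1, add the group-by-time interaction. Report the survivor-minus-control contrast at T1, T2 and T3 and the survivors' own change from T1 to T3, all from that model. Rest any claim of long-term dysbiosis on the T3 contrast.
- Say that Objectives 2 and 3, which reuse the model, follow the same specification.
- In Sample size and power, state that 0.80 applies to one group contrast with complete data, say which contrast that is, and state that it does not apply to significance at all three visits.

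The cost is wording and a few extra model outputs, with no new participants, visits or assays. The statistical price is some precision. Under equal correlations and complete data, the averaged effect has a standard error √[(1 + 2ρ)/3] times that of a single-visit contrast: 0.73 at ρ = 0.3, 0.82 at 0.5 and 0.97 at 0.9. The averaged effect can still be reported alongside. As step 6 shows, the interaction may have little power when the gap only narrows, so a non-significant interaction should not be read as persistence; the visit estimates and their intervals should carry the interpretation.

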**Methods:**

This longitudinal study investigates chemotherapy induced long-term gut dysbiosis, and associations between gut microbiota, and immune, metabolic, cognitive and psychological parameters using data collected at < 2 month (T1), 3–4 months (T2), and 5–6 months (T3) post-chemotherapy. Participants will be 18–39 year old blood or solid tumor cancer survivors (*n* = 50), and a healthy sibling, partner or friend as a control (*n* = 50). Gut microbiota composition will be measured from fecal samples using 16 s RNA sequencing. Psychological and cognitive patient reported outcome measures will include depression, anxiety, post-traumatic stress disorder symptoms, pain, fatigue, and social and cognitive function. Dual-energy X-ray Absorptiometry (DXA) will be used to measure fat and lean mass, and bone mineral concentration. Pro-inflammatory cytokines, C-reactive protein (CRP), lipopolysaccharide (LPS), serotonin, and brain derived neurotrophic factor (BDNF) will be measured in serum, and long-term cortisol will be assayed from hair. Regression and linear mixed model (LMM) analyses will examine associations across time points (T1 – T3), between groups, and covariates with gut microbiota, cognitive, psychological, and physiological parameters.

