### Procedure

Once identified, participants will be contacted by telephone or email to further verify inclusion and exclusion criteria, to obtain written informed consent, and schedule their first appointment. We will aim to assess participants at 3 different time points: < 2 months (T1), 3/4 (T2) and 5/6 (T3) months post chemotherapy, with healthy controls ideally being tested on the same day or within 5 days from when the patient is tested.

Participants will then receive a package via mail or in person, with instructions and materials for stool sample collection, and a link to fill out the self-report questionnaires, and demographic and clinical data online using REDCap. REDCap is a free, secure, browser-based application designed to support Electronic Data Capture for research studies provided through the Clinical Research Unit in the Cumming School of Medicine at the University of Calgary. Medical charts will also be accessed to confirm information regarding cancer diagnosis, treatment, glucocorticoid and antibiotic medication use, and mucositis.

Participants will be instructed to collect stool samples at home which can be stored in a freezer up to 3 days prior to their appointment, and to complete their online questionnaires prior to the appointment. On the day of their appointment, we will collect their stool sample from them. Participants will then be taken to have a hair sample collected for cortisol analysis (approximately 10 min), complete the cognitive task (i.e. the SART) on a computer (approximately 6 min), and complete their DXA scan (approximately 10 min), and have their blood drawn for serum biomarker analyses (approximately 10 min). This whole process should take approximately 45 min. Participants’ T2 and T3 month follow-up appointments will be scheduled at each subsequent visit and the procedure will be the same with respect to psychological and cognitive measures completed online, followed by their in person testing and biological sample collection. Participants will be provided a voucher for parking, and may choose from compensation in the form of either $30 at the end of the study or a pass to a fitness class after each appointment (they will have options to choose from in advance). If desired, participants will also receive a package with their individual results summarized and interpreted at the end of the study.

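### The mixed model has no survivor-control pair term although each control is linked to a particular survivor, so standard errors for average group differences are probably too wide

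*Protocol article*

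**What the plan says.** The abstract (Methods) describes the comparison group as "a healthy sibling, partner or friend as a control". The inclusion criteria for controls define eligibility by the relationship to the patient: a sibling, someone who lives with the patient, or a close friend. The Procedure section has three visits after chemotherapy, "with healthy controls ideally being tested on the same day or within 5 days from when the patient is tested".

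The Data analysis section gives the model under Objective 1: group and time are the fixed factors, and "individual subject will be a random factor". Objectives 2 and 3 test their group differences "using LMM as described above". No pair, family or household term and no matched analysis appears anywhere in the article.

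The Sample size and power section sets "Target sample sizes of at least *n* = 50 cancer survivors and *n* = 50 healthy controls", with Cohen's d = 0.5, "estimated with a power of 0.80, alpha = 0.05", and a one-sided test that survivors have lower alpha diversity.

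**The concern.** Choosing controls through the survivors links the observations in twos. The article itself lists diet, birth delivery mode and infant breastfeeding among the factors known to affect the gut microbiota. Cohabitants may share the first, and siblings may share the other two. A subject random intercept accounts for repeated visits by one person. It cannot represent similarity between two people.

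If that similarity is positive, the true variance of the average group difference is smaller than the model assumes. Intervals come out too wide, and the benefit of recruiting linked controls is not collected. The average difference in alpha diversity is the primary hypothesis, in a sample that the Discussion itself calls relatively small.

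**Working it through.** **Inputs.** From the Sample size and power section: n = 50 per group, d = 0.5 (SD = 1), one-sided alpha 0.05, power 0.80. From Data analysis: subject as the random factor. The within-pair correlation ρ is not in the article, so a range is assumed.

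**Reproducing the stated figure.** For two independent groups, SE = √(2/50) = 0.200. Power = Φ(0.5/0.200 − 1.645) = Φ(0.855) = 0.804; the exact noncentral t value is 0.799. The required n is 50 per group. The two-sided version would need 63 per group. The stated figure is therefore the one-sided, independent-groups calculation, and it is correct as such.

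**Effect of pairing, one measurement per person, 50 complete pairs.**

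- True SE = √(2(1 − ρ)/50).
- SE used when pairs are ignored = √(2/50) = 0.200.
- Ratio of used to true SE = 1/√(1 − ρ).
- Actual size when pairs are ignored = Φ(−1.645 × 0.200 / true SE).
- Power ignoring pairs = Φ((0.5 − 1.645 × 0.200) / true SE).
- Power using pairs = Φ(0.5 / true SE − 1.645).

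Example at ρ = 0.3: true SE = √0.028 = 0.167 and ratio 1.195. Size = Φ(−0.329/0.1673) = 0.025. Power is Φ(0.171/0.1673) = 0.847 ignoring pairs and Φ(2.988 − 1.645) = 0.910 using them.

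| Assumed ρ | SE ratio | Actual size | Power, pairs ignored | Power, pairs used | Pairs used, exact t (49 df) |
|---|---|---|---|---|---|
| 0 | 1.000 | 0.050 | 0.804 | 0.804 | 0.794 |
| 0.1 | 1.054 | 0.042 | 0.816 | 0.839 | 0.830 |
| 0.2 | 1.118 | 0.033 | 0.830 | 0.875 | 0.867 |
| 0.3 | 1.195 | 0.025 | 0.847 | 0.910 | 0.903 |
| 0.4 | 1.291 | 0.017 | 0.865 | 0.943 | 0.938 |

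With t rather than normal critical values, power ignoring pairs falls slightly, to about 0.81 at ρ = 0.1 and 0.86 at ρ = 0.4. At ρ = −0.1 the error reverses: SE ratio 0.95, actual size 0.058.

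**Three visits.** Assume variances of 0.3 for pair, 0.3 for subject within pair and 0.4 for residual.

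- True SE of the average group difference = √(2(0.3 + 0.4/3)/50) = 0.132.
- SE with a subject effect only = √(2(0.6 + 0.4/3)/50) = 0.171.
- The ratio is 1.30, because averaging over visits raises the correlation of subject means to 0.3/(0.6 + 0.4/3) = 0.41.

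A simulation of 20,000 balanced datasets agrees: empirical SD 0.131, subject-only SE 0.171, pair-based SE 0.131, and one-sided type I error 0.015 against 0.048.

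**Group-by-time.** For the T3 − T1 change the pair and subject effects cancel. The SE is √(2 × 0.8/50) = 0.179, whichever analysis is used. The simulation gave about 0.178 under both, matching the empirical SD.

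**The case against.** Several points on the other side are sound.

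- **Size of the correlation.** The article gives none. A friend need share neither genes nor home, a partner shares no genes, and an adult sibling may live elsewhere. Close visit dates are only an ideal. The average correlation could be small, and it may differ across microbiota, cytokine, DXA and questionnaire outcomes. This limits confidence in the magnitude; it does not remove the link between each control and a particular patient.
- **Direction.** A reader might infer that p-values are too small and false positives inflated. The figures show the opposite for positive correlation.
- **Reach.** A reader might infer that every group comparison is affected. Contrasts in change over time are not, if the pair effect is constant.
- **Sample size.** A reader might infer that the power statement is wrong. It reproduces, and at ρ from 0 upwards the planned analysis delivers about 0.80 or more. Sizing on independent groups is cautious when ρ is unknown.
- **Condensed article.** The random structure is given in one sentence, without the word *only*, and the study is described as exploratory. A fuller document may say more. But the article names both the fixed and the random factors, so this is a stated structure that does not fit the stated design, and not a detail left for later.

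**Conclusion.** The point holds for the average, between-subject survivor-control difference in Objectives 1 to 3. The stated model treats linked people as independent. Where pair members are positively correlated, its standard errors are too wide and its test is conservative. The cost is efficiency: at an assumed ρ of 0.1 to 0.4, up to about 0.08 of power at d = 0.5 (0.86 against 0.94 at the top of the range) and about 0.02 at the bottom. At ρ = 0 the difference is a few degrees of freedom.

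These figures assume complete pairs and a common correlation. Survivors without a control, or weakly correlated friends, would reduce the effect. The article does not support a claim of inflated error rates, of an inadequate sample size, or of error in the group-by-time contrasts. It is worth correcting because the loss falls on the primary hypothesis and the remedy is nearly free.

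**What to change.** Add a survivor-control pair random intercept, with subject nested in pair, to the mixed models in Objectives 1 to 3. Keep participants whose partner is missing; the mixed model allows this. Carry the pair term into any association model that pools survivors and controls. Leave the sample size as it is.

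The cost is one variance component and a pair identifier, which should be available because controls are recruited through their relationship to a patient. There are two small drawbacks. A few degrees of freedom are lost if the correlation is near zero. The random intercept also imposes one common, non-negative correlation across siblings, cohabitants and friends. If an outcome suggests otherwise, a pair-level covariance structure or cluster-robust standard errors by pair can be used instead.

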### Demographics and clinical data

Clinical and demographic factors including current age, age at diagnosis, income, occupation, ethnicity, education, living arrangements, cancer diagnosis and treatments received, history of treatment related mucositis, current diet and exercise regimes, bowel habits, glucocorticoid medication, antibiotic, and probiotic use within the last 2 years, smoking, birth delivery mode (i.e. caesarian section vs. vaginal), and breastfeeding during infancy will be collected as these variables are known to impact the gut microbiota.

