### Biomarker outcomes

*Pro-inflammatory cytokines* interleukin 6 (IL-6), interleukin 1 beta (IL-1ß), and tumour necrosis factor alpha (TNF-α), anti-inflammatory cytokine interleukin 10 (IL-10), and C-reactive protein (CRP) will be measured in serum using MesoScale multiplexing [50], in consideration of the robust plate to plate reproducibility over time and the dynamic range with a lower limit of detection in the sub picograms per milliliter (i.e. pg/mL) range.

*BDNF* will be assayed from blood serum using MesoScale multiplexing [50], in consideration of the robust plate to plate reproducibility over time and the dynamic range with a lower limit of detection in the sub picograms per milliliter (i.e. pg/mL) range.

*Serotonin* will be measured using Serotonin ELISA (enzyme-linked immunosorbent assay) kits from Enzo Life Sciences [51] according to manufactures instructions. The ELISA is a plate-based assay technique designed for detecting and quantifying substances, including neurotransmitters and proteins.

*Lipopolysacchide* (LPS), a gram-negative bacterial endotoxin associated with intestinal permeability, systemic inflammation, and sickness behaviours, will be measured from serum using MesoScale multiplexing [50].

*Cortisol* will be analyzed using hair samples, which provide a reliable and valid measure of long-term cortisol activity [52, 53]. Hair cortisol will be quantified using liquid chromatography tandem mass spectrometry, and is reported to be more representative of total cortisol production relative to single saliva or serum measures, allowing us to quantify cortisol production over an extended period of time.

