## Discussion

Using the Microbiota-Gut-Brain Axis model and the biopsychosocial framework, this research aims to elucidate the long-term effects of chemotherapy on gut microbiota, and psychological, cognitive, metabolic, and immune outcomes in young adult cancer survivors. Moreover, this study will allow us to systematically explore and validate aspects the novel model proposed here; the Chemotherapy Driven Dysbiosis of the Microbiota-Gut-Brain Axis Model.

The design of this study is not without its limitations and we have taken steps to reduce potential confounds and bias. Although the sample size of this study is relatively small, it is comparable to other studies examining the effects of chemotherapy on gut microbiota, and taking into account feasibility, this sample size will produce adequate statistical power. Furthermore, while most studies typically require participants to have not taken antibiotics for at least 3 months prior to fecal collection, we have set the required time at 1 month. This is to account for the health status of the clinical population, tight timing between follow-up appointments, and to reduce potential attrition. Although colorectal cancers do frequently occur in young adults, we have chosen to exclude this specific diagnosis type from our sample as previous research suggests that specific changes in gut microbiota may be involved in the onset and/or progression of colorectal cancer [56, 57], and therefore present a potential confounding variable. Taking into consideration that the first data collection time point is very close to the final chemotherapy treatment, it is possible that hair sample collection may not be feasible for all patients, in which case hair samples may only be collected at time points 2 and 3 for some patients. However, this should still allow us to examine changes in cortisol over 3-4 and 5- 6 months post-chemotherapy since hair cortisol allows for retrospective cortisol quantification. Finally, as this novel study is exploratory in nature, we think that the methodological plan outlined will provide a rich and varied data set with which we will be able to answer our research questions. This knowledge will ultimately be used to inform future, larger studies and, most importantly, interventions.

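### The survivor-control models for cortisol, cytokines and body composition are described without glucocorticoid exposure, and early hair samples may cover chemotherapy months, so these contrasts and the cortisol trend may be confounded

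*Protocol article*

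**What the plan says.** The model is set out under Objective 1 of the Data analysis section: "Group (survivors vs. healthy controls) and time (T1 – T3) will be fixed factors and individual subject will be a random factor". Objective 2 reuses it as its first step, to test "group differences in gut microbiota, cytokines, LPS, 5-HT and BDNF, cortisol, and body composition using LMM as described above". Correlations follow, and then regressions: "Then multivariate regression models regressing cytokines, cortisol and body composition on gut microbiota diversity will be conducted". The covariate list comes after that regression sentence: "Covariates included theoretically based on the literature will include type of cancer diagnosis (i.e. blood or solid tumor), history of mucositis, glucocorticoid medication, antibiotic", continuing with probiotic use, birth delivery mode and breastfeeding in infancy. The abstract mentions covariates more loosely: "Regression and linear mixed model (LMM) analyses will examine associations across time points (T1 – T3), between groups, and covariates with gut microbiota".

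The Demographics and clinical data section collects "glucocorticoid medication, antibiotic, and probiotic use within the last 2 years", and the Procedure section has glucocorticoid use confirmed from medical charts. Neither exclusion list mentions glucocorticoids.

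Under Biomarker outcomes, hair is chosen for cortisol as "allowing us to quantify cortisol production over an extended period of time". The Discussion adds that "hair cortisol allows for retrospective cortisol quantification". No segment length or look-back period is given. Visits are at under 2 months (T1), 3 to 4 months (T2) and 5 to 6 months (T3) after chemotherapy.

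**The concern.** The protocol treats glucocorticoids as relevant enough to record, verify and adjust for, yet leaves them out of the model that first compares survivors with controls on cortisol, cytokines and body composition. If exposure differs between the groups and affects these outcomes, the group term carries both the after-effects of chemotherapy and the effect of the medication.

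For cortisol there is a second problem, of timing. A hair sample represents past months, not the visit date. A sample labelled as post-chemotherapy can partly measure the chemotherapy period, and the share changes from visit to visit. A change from T1 to T3 could then reflect treatment months leaving the window rather than a change in HPA-axis function after chemotherapy. The Discussion treats T1 hair only as a question of feasibility and does not address this.

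**Working it through.** **The plan's own figure.** No figure is given for cortisol, cytokines or body composition. The only calculation is for alpha diversity: 50 per group, d = 0.5, one-sided alpha 0.05, power 0.80. It reproduces: 50 per group, power 0.804 by the normal approximation and 0.799 by the t distribution. It has no bearing on this point.

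**Which model holds which term.**

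| Step in Objective 2 | Terms named | Glucocorticoids |
|---|---|---|
| Group-difference LMM | group, time, subject | not named |
| Regression on gut diversity | diversity plus covariate list | named |

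The list cannot be carried whole into the LMM. It includes cancer type, which is undefined for controls because a personal history of cancer excludes them, and history of mucositis, which is recorded as treatment-related.

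**Share of the hair window that falls before the last chemotherapy.** For a window of L months sampled t months after chemotherapy, share = max(0, L − t)/L. L is an assumption; t comes from the visit schedule. Example: L = 3, t = 0.5 gives 2.5/3 = 83%.

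| Assumed L | t = 0.5 (T1) | t = 1 (T1) | t = 2 (T1 limit) | t = 3 (T2) | t = 4 (T2) | t = 5 (T3) | t = 6 (T3) |
|---|---|---|---|---|---|---|---|
| 1 month | 50% | 0% | 0% | 0% | 0% | 0% | 0% |
| 3 months | 83% | 67% | 33% | 0% | 0% | 0% | 0% |
| 6 months | 92% | 83% | 67% | 50% | 33% | 17% | 0% |

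A survivor seen at 0.5, 3 and 5 months would have shares of 83%, 0% and 0% with a 3-month window, and 92%, 50% and 17% with a 6-month window. Either pattern puts a treatment gradient into the T1 to T3 trend.

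**How far confounding could move a group contrast.** Let p be the excess proportion of survivors exposed and s the shift in the outcome in SD units, both assumed. With no true difference, the spurious difference is d = p × s. With 50 per group at one time point, the standard error is √(2/50) = 0.2, and the two-sided 5% rejection probability is Φ(d/0.2 − 1.96) + Φ(−d/0.2 − 1.96).

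| p | s | d | Rejection probability |
|---|---|---|---|
| 10% | 0.3 | 0.03 | 5.3% |
| 30% | 0.5 | 0.15 | 11.7% |
| 50% | 1.0 | 0.50 | 70.5% |
| 80% | 1.0 | 0.80 | 97.9% |

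The range runs from negligible to dominant. The article gives nothing that places the study within it.

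**The case against.** The strongest reply is that the main cortisol hypothesis is largely outside this point. Hypothesis (ii) links gut dysbiosis to higher cortisol within survivors. It is tested by the regression on diversity, where glucocorticoid medication is listed, and Objective 4 relates clinical factors to the same outcomes. The LMM is a preliminary step in a study that calls itself exploratory and whose primary hypothesis is alpha diversity. All of that stands, and it limits the point to the group contrasts and the cortisol trend.

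It can also be said that the covariate sentence closes the Objective 2 paragraph without being expressly limited to the regressions, that the abstract names covariates alongside the LMM, and that a condensed article may leave details to a fuller plan. This has some force: the safe statement is that the LMM as described names no such covariate. But the article does state the model's terms, and the list as written does not fit a survivor-control comparison.

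The words about the last 2 years may qualify only antibiotic and probiotic use, and the data form is not shown. So it is not established that the timing of glucocorticoid use will be unknown. If the 2-year look-back does apply, it cannot by itself place exposure inside or outside a hair window.

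Finally, where glucocorticoids belong to a regimen, adjusting for them removes part of the exposure under study. That is a reason to present the restricted comparison as a sensitivity analysis.

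**Conclusion.** The point holds in a limited form. As described, the group contrasts in cortisol, cytokines and body composition cannot be separated from glucocorticoid exposure, and cortisol at T1 will include treatment months whenever the hair window exceeds the time since chemotherapy. The shares in the table depend on the assumed window, and the size of the bias depends on exposure and effect figures that the article does not give.

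Three stronger readings are not supported:

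- A reader might infer that the cortisol result will reflect steroid treatment rather than HPA-axis function. The article gives no prevalence, effect size or direction, so it supports only that the result may be confounded.
- A reader might take hypothesis (ii) as predicting higher cortisol in survivors than in controls. It is worded as an association with dysbiosis in survivors, and its regression lists glucocorticoid medication, so that test is less affected.
- A reader might assume that T2 and T3 hair is free of treatment months. That is true for a window of up to 3 months, but not for 6.

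The change is worth making, since it is cheap, but it does not touch the primary hypothesis.

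**What to change.** - State the hair segment to be assayed and the calendar period it represents at each visit.
- Take the dates of glucocorticoid use from the charts that are already being opened.
- Base the post-chemotherapy cortisol contrast and trend on samples whose window begins after the last chemotherapy. Report the other samples separately as covering treatment. Define this by window and date, not by visit label.
- For cortisol, cytokines and body composition, add a sensitivity LMM comparing controls with survivor samples unexposed to glucocorticoids in the relevant window, with that window specified in advance for each outcome. A covariate alone is a weak remedy: if few controls are exposed, which is an assumption, it is largely collinear with group and is estimated mainly within survivors.
- Say explicitly whether any of the listed covariates enter the group-comparison LMM.

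The cost is some additional chart extraction and analysis, with no new assay. The main cortisol contrast loses samples, mostly at T1. The Discussion already expects some survivors to have no T1 hair, but this rule could remove T1 samples from more of them.
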